##### PHQ-9 Instrument

This widely used self-report measure assesses symptoms of depression with 9 items that correspond to the symptoms of major depression described in the *Diagnostic and Statistical Manual of Mental Disorders, Fifth Edition* [18], on a 4-point Likert scale [32,33]. Higher scores indicate more severe depressive symptoms. The PHQ-9 has shown good internal consistency as well as good sensitivity and specificity [33,43,44].

##### 12-Item Short Form Health Survey

This self-report instrument measures quality of life. It has 2 subscales measuring physical and mental aspects of health-related quality of life with a total of 12 items. The 12-Item Short Form Health Survey has shown good psychometric properties, roughly equivalent to those of the 36-Item Short Form Health Survey, and is widely used as an estimate of general quality of life [37,45].

##### Internalized Stigma of Mental Illness Scale

This 29-item self-report scale [38,46] measures the internalized stigma of mental illness. It is widely used in various contexts and consists of 5 subscales: alienation, stereotype endorsement, discrimination experience, social withdrawal, and stigma resistance. It has shown good internal consistency and good test-retest reliability [38]. Often, the stigma resistance subscale is excluded in analyses as some researchers have suggested that another construct be measured using this subscale [47]. As suggested by these researchers, preliminary factor analysis will be conducted to decide whether to include this subscale in the total score.

##### Inventory of Attitudes Toward Seeking Mental Health Services

This 24-item self-report scale [39,48] measures the participants’ attitudes toward seeking help for mental health issues. It is an adaptation of an older scale [49] and has 3 subscales. This scale is used in nonclinical as well as clinical samples. The German version has shown acceptable psychometric properties [39].

##### Level of Personality Functioning Scale–Brief Form 2.0

This 12-item self-report tool [40,50,51] measures the impairment in self-functioning regarding sense of self and interpersonal functioning based on the Alternative DSM-5 Model of Personality Disorders [18]. The questions are answered on a 4-point Likert scale (1=“does not apply at all”; 4=“applies exactly”). It consists of 2 subscales and is a fairly new tool. A thorough validation for clinical samples is still pending, but good internal consistency for the German scale has already been determined [40].

##### Preference

Preference will be assessed by presenting all participants with 2 approximately 150-word texts describing the 2 versions of the program. They will then be asked to indicate their preference and their preference strength by answering the question “How important is this choice to you?” on a 4-point Likert scale (1=“not important at all”; 4=“very important”), as done previously [52]. Participants are only forced to make a choice at preassessment to enable possible condition allocation for all participants that are randomized to the preference condition. At the remaining measurement points, participants can indicate that they have no preference.

##### Engagement

When it comes to engagement, “the more use the better” is not always true [53], especially for internet interventions such as this one, where the participants determine the dosage themselves. However, given that one version will be completely anonymous, it will not be possible to use complex measures of engagement for individual participants in this condition at a technological level. To find a compromise and gain insights into program use, the total number of clicks during the intervention period will be recorded for both program versions and then divided by the number of participants per version, providing an average that can be compared between groups. This has been done before for other internet interventions [54].

### Power Analysis

This study is powered regarding the primary outcome (composite score of the SPS and SIAS) and first study aim (whether anonymous digital interventions are less efficacious than conventional, nonanonymous programs). This means the comparison of the 2 versions in terms of reduction in SA symptoms in the randomized condition. As we expect a superiority of the nonanonymous version, a Cohen *d* value of 0.35 was used as the target effect size between groups as we considered smaller effects clinically insignificant. We conducted a power analysis for Cohen *d*=0.35 with an α level of .05 and a power of 0.80 for the time × group interaction. The sample size was determined using the ANOVA power Shiny app [55], which is based on the R programming environment [56], and the *Superpower* package for R (R Foundation for Statistical Computing). This app performs Monte Carlo simulations tailored to factorial experimental designs, allowing for interaction effects and comparisons across both within- and between-subject factors [55]. For the power analysis, we defined the randomized condition as a mixed 2 × 3 design with 2 program versions (between) and 3 time points (within). For means and SDs of the nonanonymous version, values from another trial with the same basic online program were taken [26], and for the anonymous version, the means were calculated using the aforementioned effect size. The SDs used were the same as in the nonanonymous version, and the correlation of within-subject factors was set at *r*=0.5. For SPS values with 2000 simulations, a total of 113 participants per condition are needed, and for SIAS values, 112 participants are needed per condition to reach 0.80 power for the interaction effect. Therefore, for the 2 randomized arms, 113 participants per arm will be recruited. Although we do not know beforehand how many participants will be in each of the 2 preference arms, we doubled the participants from the randomized arm for the power analysis, resulting in a total of 452 participants across all 4 arms.

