### Statistical Analysis

We will evaluate the differences in SA symptom change between the anonymous version (JOURNeY_A) and the nonanonymous version (JOURNeY_NonA) using linear mixed models with the posttreatment assessment as the confirmatory primary end point. Time will be used as the within-subject factor, and condition will be used as the between-subject factor. Fixed effects will be time, condition (JOURNeY_A or JOURNeY_NonA), and the intervention term; the random effect will be the intercept of each participant as every participant is expected to have a different prescore. This analysis accounts for the correlation of residual errors within participants and includes a treatment-by-time interaction term to assess differential symptom change over time [57]. Estimates for each time point will be derived from this model. We will conduct the analysis based on the intention-to-treat principle. The intention-to-treat analysis set consists of all participants in the randomized group regardless of any protocol violations. The inferences about overall program efficacy will only be made based on the randomized arm. For the exploratory preference analysis, appropriate methods such as multiple logistic regression, *t* tests, and chi-square tests will be used depending on the type of data. Comparisons will focus, for example, on participants who received their preferred treatment (preference match) versus those who did not (preference not matched). The amount and pattern of missing data will be reported, and results will be interpreted accordingly in a cautious manner. To allow for comparison across trials, we will also report the standardized mean differences (effect sizes).

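### The randomized arms recruit exactly the number simulated as needed for 0.80 power, with no allowance for missing follow-up, so 0.80 appears to be a complete-data figure

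*Protocol article*

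**What the plan says.** The Power Analysis section of the protocol article sizes the trial "with an α level of .05 and a power of 0.80 for the time × group interaction". A Cohen d of 0.35 "was used as the target effect size between groups as we considered smaller effects clinically insignificant". The randomized condition was simulated as two versions by three time points with a within-subject correlation of 0.5. On the inputs it adds: "For means and SDs of the nonanonymous version, values from another trial with the same basic online program were taken", and for the anonymous arm, "The SDs used were the same as in the nonanonymous version". The source figures are not printed.

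For the SPS, "a total of 113 participants per condition are needed"; for the SIAS the figure is 112. The conclusion follows directly: "Therefore, for the 2 randomized arms, 113 participants per arm will be recruited". The Participants section repeats 113 per version. The total of 452 comes from doubling the randomized number to cover the preference condition.

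The Statistical Analysis section makes week 8 the confirmatory end point, plans a random-intercept linear mixed model by intention to treat, and bases efficacy inference on the randomized arm only. On missing data it says: "The amount and pattern of missing data will be reported, and results will be interpreted accordingly in a cautious manner".

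**The concern.** A sample size for a stated power is normally raised to allow for participants who do not supply the outcome. Here nothing is added between the number needed and the number recruited, and no expected retention is given. The preference arms cannot make up losses, because they are excluded from efficacy inference.

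Some non-response is likely. The program is unguided, its use is left to the participant, questionnaires go out by automatic email, and no compensation is offered. The article promises to report missing data but does not connect them to power.

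The trial asks whether the anonymous version is less efficacious, and the article calls effects below 0.35 clinically insignificant. A non-significant result could therefore be read as showing no important loss of efficacy. How far that reading can go depends on whether power was 0.80 or appreciably lower.

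**Working it through.** **Inputs from the article.** α = 0.05, power 0.80, d = 0.35, three time points, r = 0.5, 113 per arm.

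**Assumptions made here.** Loss rates (none is given); equal SDs over time; a group difference of 0 at baseline and 0.35 at weeks 8 and 24.

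**1. The plan's own figure.** With complete data the interaction F test has 2 and 2(2n − 2) degrees of freedom and noncentrality

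λ = (n/2) · Σ(d_t − mean d)² / (1 − r) = n d² / 1.5.

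At n = 113, λ = 113 × 0.1225 / 1.5 = 9.23 and power is 0.779; 0.80 needs 119 per arm. The figure of 113 cannot be reproduced exactly because the means and SDs are not printed. If SDs grow by 5 to 15% over time (assumed), simulated power at 113 is 0.805 to 0.821. So 113 is plausible as a complete-data number, and nothing suggests an allowance hidden in it.

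**2. Loss after baseline, interaction test, anchored at the stated 0.80.** Power of 0.80 with 2 and 448 degrees of freedom needs λ = 9.70. Let q be the share retained, with the others contributing baseline only. The mixed model uses those baseline records. For this effect pattern the per-arm variance of the mean follow-up minus baseline is 0.5/(nq) + 0.25/n in units of σ², against 0.75/n with complete data. So λ is multiplied by 0.75 / (0.5/q + 0.25) = 3q/(2 + q), and the effect detectable with 0.80 power is 0.35 divided by the square root of that factor.

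| Retained | Factor | λ | Power | Detectable d |
|---|---|---|---|---|
| 100% | 1 | 9.70 | 0.80 | 0.35 |
| 90% | 0.931 | 9.03 | 0.77 | 0.36 |
| 80% | 0.857 | 8.31 | 0.73 | 0.38 |
| 70% | 0.778 | 7.54 | 0.69 | 0.40 |
| 60% | 0.692 | 6.71 | 0.63 | 0.42 |

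At 1% loss power is 0.797. The Monte Carlo standard error with 2000 runs is √(0.8 × 0.2 / 2000) = 0.009, so one or two losses cannot be told apart from simulation error. If week 8 is missing but week 24 is present, the interaction test loses less: 0.790, 0.780 and 0.769 at 10, 20 and 30%.

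**3. Week-8 contrast alone, equal SDs, not anchored.** The per-arm variance of the change from baseline to week 8 is 0.75/(nq) + 0.25/n. With complete data λ = 0.1225 / (2/113) = 6.92 and power is about 0.745. At 10, 20, 30 and 40% loss it is about 0.71, 0.67, 0.62 and 0.57.

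**4. Week-8 contrast with a common baseline mean or baseline adjustment.** The variance of the difference is 2(1 − r²)/n = 1.5/n, where n is now the number with week-8 data.

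| n per arm | λ = 0.1225 n / 1.5 | Power | Detectable d = 2.80 √(1.5/n) |
|---|---|---|---|
| 113 | 9.23 | 0.86 | 0.32 |
| 102 | 8.33 | 0.82 | 0.34 |
| 90 | 7.35 | 0.77 | 0.36 |
| 79 | 6.45 | 0.71 | 0.39 |
| 68 | 5.55 | 0.65 | 0.42 |

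These rows compare with step 3, not step 2, because both concern week 8 only.

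**The case against.** Nothing is miscalculated: 113 is stated as needed, 113 is recruited, and 4 × 113 = 452. The article does not use the words complete data; that is inferred from its silence on missingness. It gives no attrition rate, so the size of the loss is assumed throughout. A true within-subject correlation above 0.5 would raise power. Recruitment has closed, and effect sizes will be reported anyway. All of this stands, and it limits the point to disclosure and choice of model.

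Three stronger readings are tempting, and the documents do not support them.

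- A reader might infer that any missing week-8 value takes power below 0.80. One or two losses fall within simulation error, and a common-baseline model still has about 0.82 for the week-8 contrast at 10% loss.
- A reader might infer that participants with only a baseline score contribute nothing. That holds for a completers-only analysis, where anchored power would be 0.754, 0.700 and 0.637 at 10, 20 and 30% loss. The planned mixed model uses their baseline values, which gives 0.769, 0.732 and 0.687.
- A reader might blame attrition for the whole gap between 0.80 and a figure near 0.60 to 0.65. With equal SDs the week-8 contrast has only about 0.745 with no loss at all. That shortfall comes from testing a single contrast instead of the simulated three-time-point interaction, and from replacing unprinted SDs with equal ones. It is a separate matter.

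**Conclusion.** The point holds as an omitted allowance. Recruitment in the randomized arms equals the number simulated as needed, nothing elsewhere offsets losses, and the stated 0.80 is best read as a complete-data figure.

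Anchored at that 0.80, with a mixed model using all records, the cost in interaction power is about 3, 7, 11 and 17 points at 10, 20, 30 and 40% loss after baseline. The existence of the gap is clear from the text. Its size rests on assumed loss rates, equal loss in both arms, r = 0.5 and an effect that is the same at weeks 8 and 24.

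**What to change.** Before any data are analysed, and without extra enrolment:

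1. State that the 0.80 assumes complete data.
2. Restate power and detectable effect at 100, 90, 80, 70 and 60% week-8 retention. The 100% row keeps the effect of attrition apart from the effect of testing one contrast. Use the means and SDs from the original simulation in place of the equal SDs assumed here.
3. Fit the mixed model with a common baseline mean across the two randomized arms, or adjust for baseline. Randomization justifies this. For the week-8 contrast it adds about 8 to 11 points at every retention level shown, though it does not restore 0.80 once loss reaches 20%.

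The cost is one sentence, one table and a small change to the model specification. The downside is a less favourable stated power.

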### Statistical Analysis

We will evaluate the differences in SA symptom change between the anonymous version (JOURNeY_A) and the nonanonymous version (JOURNeY_NonA) using linear mixed models with the posttreatment assessment as the confirmatory primary end point. Time will be used as the within-subject factor, and condition will be used as the between-subject factor. Fixed effects will be time, condition (JOURNeY_A or JOURNeY_NonA), and the intervention term; the random effect will be the intercept of each participant as every participant is expected to have a different prescore. This analysis accounts for the correlation of residual errors within participants and includes a treatment-by-time interaction term to assess differential symptom change over time [57]. Estimates for each time point will be derived from this model. We will conduct the analysis based on the intention-to-treat principle. The intention-to-treat analysis set consists of all participants in the randomized group regardless of any protocol violations. The inferences about overall program efficacy will only be made based on the randomized arm. For the exploratory preference analysis, appropriate methods such as multiple logistic regression, *t* tests, and chi-square tests will be used depending on the type of data. Comparisons will focus, for example, on participants who received their preferred treatment (preference match) versus those who did not (preference not matched). The amount and pattern of missing data will be reported, and results will be interpreted accordingly in a cautious manner. To allow for comparison across trials, we will also report the standardized mean differences (effect sizes).

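### The primary model leaves baseline means free to differ between randomized arms; a common baseline mean would cut the week-8 variance by a quarter and raise power from about 0.745 to 0.86

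*Protocol article*

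**What the plan says.** The Statistical Analysis section of the protocol article sets out a linear mixed model for the social anxiety composite, with the week-8 assessment as the confirmatory endpoint. The terms are "Fixed effects will be time, condition (JOURNeY_A or JOURNeY_NonA), and the intervention term". The last term is evidently the interaction, since the same paragraph goes on to describe a treatment-by-time term. The only random effect is a participant intercept. The pre-treatment score enters as one of three levels of time; neither a baseline covariate nor an equal-baseline constraint is mentioned. Inference on efficacy is confined to the randomized participants.

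The Power Analysis section gives the planning inputs: "a Cohen *d* value of 0.35 was used as the target effect size between groups"; "the correlation of within-subject factors was set at *r*=0.5"; and "for the 2 randomized arms, 113 participants per arm will be recruited". The calculation was made "with an α level of .05 and a power of 0.80 for the time × group interaction".

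Under Procedures, candidates are screened on the self-report measures before assignment, and those in the randomization condition are then allocated to a version with equal probability. Under Participants, eligibility requires a score above the cutoff on the SPS or the SIAS.

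**The concern.** In the randomized arms the baseline is measured before allocation, so the two versions have the same expected baseline mean. A free condition main effect ignores this. It fits each arm's observed baseline mean exactly, and the week-8 interaction then subtracts the two baselines in full. Any chance gap at baseline is carried into the treatment effect, when it could be used to reduce its variance. The random intercept does not help: it models correlation within participants, but with complete data the interaction estimate is still the raw difference in change. If the primary estimate is instead read as the model's week-8 mean difference, it is the raw week-8 difference, which makes no use of baseline at all.

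Recruitment has ended, so the choice of model is the main lever left on precision. The article powers the trial on its primary outcome, defined at week 8, but the 0.80 it states is for an interaction over three time points, and 113 is not inflated for dropout. A null result for lack of precision could be misread as showing that the anonymous version is no less efficacious, which is the trial's main question.

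**Working it through.** **Inputs.** From Power Analysis: d = 0.35, r = 0.5, α = 0.05, n = 113 per arm, equal SDs in the two versions ("The SDs used were the same as in the nonanonymous version"). From Statistical Analysis: week 8 as the contrast, random intercept only. Assumed because the article does not say: two-sided testing, the same SD σ at every time point (the values come from a cited trial and are not given), and complete data. The last two are varied below, and sidedness is taken up under the objections.

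**The plan's own figure.** For the 2-df interaction in the 2 × 3 design, with version differences of (0, 0.35, 0.35) SD, the noncentrality is λ = (n/2)·Σ(d_t − d̄)²/(1 − r). This gives power of 0.779 at n = 113; 119 per arm would be needed for 0.80. With post-baseline SDs about 8% above the baseline SD, simulated power at 113 is 0.81. The stated 113 is therefore plausible, but cannot be confirmed without the means and SDs.

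**Variance of the week-8 effect, per-person factor.**
- Model as written (difference in change): 2(1 − r)σ² = 1.00σ².
- Common baseline mean: (1 − r²)σ² = 0.75σ².
- Ratio: (1 − r²)/[2(1 − r)] = (1 + r)/2 = 0.75.

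A generalized least squares calculation for the full three-time-point random-intercept model agrees: 0.01770 (= 2 × 1.00/113) as written and 0.01327 (= 2 × 0.75/113) with the constraint, in units of σ². The week-24 data do not change this, because their treatment effect is also free.

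**Power at 113 per arm.**
- As written: noncentrality 0.35/√0.01770 = 2.63; power 0.745 (noncentral t).
- Constrained: 0.35/√0.01327 = 3.04; power 0.857.
- 10,000 simulated trials, with the constraint represented by baseline-adjusted analysis: 0.748 and 0.854.
- Equivalent sample size: 113/0.75 = 151 per arm.
- n per arm for 0.80 power (normal approximation): 129 as written, 97 constrained.

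At r = 0.5 the raw week-8 difference also has factor 1.00σ², so 0.745 holds under either reading of the primary contrast.

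**Sensitivity to r (change contrast, complete data, equal SDs).**

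| r | Variance reduction | Power as written | Power constrained |
|---|---|---|---|
| 0.3 | 35% | 0.60 | 0.78 |
| 0.4 | 30% | 0.67 | 0.82 |
| 0.5 | 25% | 0.745 | 0.857 |
| 0.6 | 20% | 0.83 | 0.91 |
| 0.7 | 15% | 0.92 | 0.96 |

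If the contrast is the raw week-8 difference, power as written stays at 0.745 for every r and the variance reduction is r²: 25% at r = 0.5, 49% at r = 0.7.

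**Sensitivity to missing week-8 data (assumed rates, r = 0.5).** With 101, 90 and 79 completers per arm (10%, 20%, 30% lost), power is 0.70 against 0.82, 0.65 against 0.77, and 0.59 against 0.71.

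**Sensitivity to unequal SDs (r = 0.5, d on the week-8 SD).** With p the baseline SD as a fraction of the week-8 SD, the change factor is p² + 1 − p, and the constrained factor stays at 0.75.
- Week-8 SD 8% larger (p = 0.926): factor 0.931, reduction 1 − 0.75/0.931 = 19.5%, power as written 0.775.
- p = 0.8: factor 0.84, reduction 1 − 0.75/0.84 = 11%, power as written 0.815.
- Power with baseline handled efficiently is 0.857 in both cases.

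**The case against.** **The model is not wrong.** It is a conventional specification, unbiased under randomization, and it matches the structure used for the sample size, so 113 per arm does not rely on precision the model fails to deliver. Details of baseline handling often belong in an SAP, which is not shown. The first part stands: this is lost efficiency, not an invalid analysis. The SAP argument is weaker, because the article does list the fixed effects, and that list leaves the baseline means free.

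**The stated 0.80 belongs to a different test.** It is for the interaction over three time points, and no power is given for the week-8 contrast alone. That is right: 0.745 and 0.80 do not show an arithmetic error. It remains true that the primary outcome is defined at week 8 and that, on the planning inputs, this contrast has less than 0.80 power.

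**The size of the gain depends on assumptions.** With a smaller baseline SD, which is plausible because entry is selected on baseline scores, the saving may be 11% to 20% instead of 25%. With r of 0.6 or 0.7 the change contrast already exceeds 0.80 power, and the gain is about 3 to 7 points. The article does not state sidedness and expects the nonanonymous version to be superior; one-sided, the figures are 0.84 and 0.92. All of this stands and limits how firmly the headline figures can be stated. None of it reverses the direction: with equal SDs the variance ratio (1 + r)/2 is below 1 for every r below 1.

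**Constraint and covariate adjustment are not identical.** They give essentially the same answer only with complete data; using baseline as a covariate drops participants with no post-baseline score. This is correct, and it favours the constrained model.

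**Conclusion.** The concern holds. As specified, the primary model discards baseline information that randomization makes safe to use. At the protocol's d = 0.35, r = 0.5 and 113 per arm, with two-sided testing, equal SDs and complete data, this costs a quarter of the achievable precision and about 11 points of power (0.745 against 0.857). Under the other values of r, SD and missingness examined, the size of the gain changes but its direction does not. The analysis as written would not be biased, so this is a change that should be made, not a fault that invalidates the trial.

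**What to change.** Specify the primary model for the randomized arms with a mean for each time point and version-by-time terms at week 8 and week 24 only, omitting the condition effect at baseline (a constrained longitudinal model). Name the week-8 version difference as the primary estimate. This form keeps every randomized participant with a baseline score, in line with the intention-to-treat set. The alternative is to model the week-8 and week-24 composites with the baseline composite by time as covariate, noting that it loses participants without post-baseline data. Stated baseline preference may be added as a covariate; no gain from that has been calculated here. The constraint must not be applied to the preference arms, where version is not randomized.

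The cost is one line in the SAP and in the model code. No participants or measurements are added, since eligibility already requires baseline SPS and SIAS. The article's Results section says no data have been analysed, so the change can still be prespecified; it should be dated and recorded before analysis begins.

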### Participants

We will recruit a total of 452 adults with increased SA symptoms, as indicated in the Power Analysis section. Therefore, in the randomization arm, there will be 113 participants per program version. The participant numbers in the preference arm will depend on the participants’ indicated preferences. Candidates will be included if they (1) are aged ≥18 years; (2) return the informed consent form; (3) have access to the internet; (4) have a smartphone, PC, or tablet; and (5) exceed cutoff scores in at least one of the 2 SA measures (>22 points on the Social Phobia Scale [SPS] or >33 points on the Social Interaction Anxiety Scale [SIAS] [30,31]). A formal diagnosis of SAD is not required, and no clinical interviews will be conducted with potential participants. Conducting in-depth and personal interviews would be incongruent with the nature of anonymous DMHIs as such procedures are rarely part of routine practice, where users typically access these tools independently and without previous interaction.

Candidates will be excluded from the study if they (1) report acute suicidality at the beginning of the study (≥2 points on suicide item 9 of the Patient Health Questionnaire–9 [PHQ-9] [32,33]) or (2) report having previously been diagnosed with psychotic symptoms or bipolar disorder.

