### Procedures

After receiving the study information and returning the signed informed consent form, the candidates will be screened for eligibility using the self-report measures described in the Instruments section. Participants will additionally be shown brief descriptions of both program versions during screening and asked to select their preferred option. If eligible, the participants will be assigned to a condition. The randomization will be performed in 2 steps to ensure correct condition allocation. In a first step, eligible candidates will be randomized with equal probability to either the randomization or preference condition. In a second step, the participants in the randomization condition will be randomized again with equal probability to one of the program versions (anonymous vs nonanonymous) regardless of previously expressed preference. The participants in the preference condition will be assigned to their preferred program version. Thus, the main effect of the treatment can be estimated, but it is also possible to explore preferences and their possible effects through the preference arm. The first randomization will be conducted using the built-in randomization tool in REDCap [28,29], where all the data will be collected, whereas the second randomization will be conducted by an external researcher with a randomization list created using randomly permutated blocks. An external researcher has to be involved in the randomization as REDCap can only perform one randomization per participant. The condition allocation will be unknown to investigators.

The intervention period, during which participants are asked to use the self-help program, will be 8 weeks. The duration of the study for 1 participant will be 24 weeks. There are 3 main measurement time points during this period: at the beginning (preassessment), after 8 weeks (postassessment), and after 24 weeks (follow-up assessment). In addition, there are 2 minor measurement points, after 3 and 6 weeks, where only preference and other measures unrelated to this part of the study will be assessed. The questionnaires will be sent out automatically through REDCap [28,29] via email at the corresponding time points.

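### A participant random intercept as the only named random effect ties the week-8 standard error to one variance and one correlation over all three visits; an unstructured covariance would remove that dependence

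*Protocol article*

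**What the plan says.** The Statistical Analysis section of the protocol article compares the two program versions "using linear mixed models with the posttreatment assessment as the confirmatory primary end point". Fixed effects are time, condition and a third term that the following text shows to be the treatment-by-time interaction. On the random part it says "the random effect will be the intercept of each participant as every participant is expected to have a different prescore". No random slope is named. The next sentence states: "This analysis accounts for the correlation of residual errors within participants". It names no residual covariance structure. The week-8 result comes from this same model: "Estimates for each time point will be derived from this model".

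The Procedures section sets the three main assessments at baseline, week 8 and week 24. The Power Analysis section assumes one common within-person correlation of 0.5. It takes SDs from an earlier trial of the same basic program but does not print them.

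**The concern.** A random intercept with ordinary residuals forces the variance to be the same at every visit and the correlation to be the same for every pair of visits. The model then has one residual variance, estimated from all three visits together. The SE for the pre-to-week-8 change therefore reflects the average behaviour of three pairs of visits, two of which involve week 24.

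The confirmatory p-value and confidence interval rest on that SE. If the pre/week-8 pair is more variable than the average pair, the SE is too small and the type I error exceeds 5%. If it is less variable, the SE is too large and the trial, planned for a power of only 0.80, loses power.

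**Working it through.** **The plan's own figure.** The Power Analysis section gives 113 per arm for 0.80 power on the time × group interaction in a 2 × 3 mixed design, at d = 0.35, r = 0.5 and α = .05. The noncentral F parameter is λ = (n/2)·Σ(centred differences)²/(1 − r). I assume equal SDs and arm differences of 0, 0.35 and 0.35. The centred squares sum to 0.0817, so λ = 56.5 × 0.0817/0.5 = 9.23 on 2 and 448 df. Power is 0.779, and 0.80 needs 119 per arm. With assumed SD ratios of 1/1.1/1.1, simulated power at 113 per arm is 0.811. So 113 is plausible but cannot be confirmed without the unprinted SDs. What matters here is that the planning input is one common correlation, which is the random-intercept structure if the SDs are also equal.

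**Inputs for the check.** From the article: three visits, 113 per randomized arm, α = .05. Assumed: a two-sided test (sidedness is not stated), complete data, and every SD and correlation other than the common r = 0.5.

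**Formulas.** Let D(a,b) = SD(a)² + SD(b)² − 2·r(a,b)·SD(a)·SD(b) be the variance of the change between two visits.
- True SE of the between-arm difference in pre-to-week-8 change: √(2·D(pre,8)/113).
- Random-intercept SE: the same expression with D(pre,8) replaced by the mean of D(pre,8), D(pre,24) and D(8,24).
- Ratio R = √(mean D / D(pre,8)). The arm size cancels.
- True level of a nominal 5% test: 2·(1 − Φ(1.96·R)).

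**Results.** Correlations are in the order pre/week 8, pre/week 24, week 8/week 24, and the D values are in the same order.

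| SDs (pre, 8, 24) | Correlations | D values | Mean D | R | True level |
|---|---|---|---|---|---|
| 1, 1, 1 | 0.5, 0.5, 0.5 | 1, 1, 1 | 1.000 | 1.000 | 5.0% |
| 1, 1, 1 | 0.7, 0.6, 0.8 | 0.6, 0.8, 0.4 | 0.600 | 1.000 | 5.0% |
| 1, 1, 1 | 0.5, 0.45, 0.7 | 1.0, 1.1, 0.6 | 0.900 | 0.949 | 6.3% |
| 1, 1, 1 | 0.5, 0.5, 0.75 | 1.0, 1.0, 0.5 | 0.833 | 0.913 | 7.4% |
| 1, 1, 1 | 0.7, 0.5, 0.7 | 0.6, 1.0, 0.6 | 0.733 | 1.106 | 3.0% |
| 0.85, 1, 1 | 0.5, 0.5, 0.5 | 0.8725, 0.8725, 1.0 | 0.915 | 1.024 | 4.5% |
| 0.85, 1, 1 | 0.5, 0.5, 0.75 | 0.8725, 0.8725, 0.5 | 0.748 | 0.926 | 6.9% |
| 1, 0.9, 0.9 | 0.6, 0.6, 0.8 | 0.73, 0.73, 0.324 | 0.595 | 0.903 | 7.7% |
| 1, 1.2, 1.3 | 0.7, 0.5, 0.7 | 0.76, 1.39, 0.946 | 1.032 | 1.165 | 2.2% |

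The last two rows are the extremes of all the patterns tried. In the last row, power for a difference of 0.35 baseline SDs at 113 per arm is 0.768, against 0.855 with the correct SE.

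**If the week-8 level is tested instead of the change.** The model then uses the mean of the three visit variances. With SDs 0.85, 1 and 1 the mean is (0.7225 + 1 + 1)/3 = 0.9075. The SE ratio is √0.9075 = 0.953 and the true level is 6.2%, whatever the correlations.

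**The case against.** **Inflation as a forecast.** A reader might infer that the type I error will be inflated. Two features of the design invite this: participants must "exceed cutoff scores in at least one of the 2 SA measures", the same scales that form the primary outcome, and scores may track more closely after treatment ends. Neither settles the direction.
- A smaller baseline SD alone makes the SE of the change contrast slightly conservative (R = 1.024, level 4.5%). In the row with baseline SD 0.85 and a level of 6.9%, the assumed 0.75 correlation causes the inflation. With equal SDs and the same correlations the level is higher, at 7.4%.
- Closer tracking between weeks 8 and 24 is not sufficient either. Correlations of 0.7, 0.6 and 0.8 have that feature and give no error. Pre and week 8 are also the closest pair in time (8 weeks, against 16 and 24), and ordinary decay of correlation with time pushes toward a conservative SE.

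This objection stands in full against any one-directional claim.

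**The sentence on residual correlation.** It can be read as announcing a further residual structure, with the detail left to an analysis plan that is not shown. That reading is possible. But the sentence names no structure, and a random intercept already induces a within-person correlation, so it may only describe the model just given. It neither contradicts the random intercept nor clearly extends it. Because the article does name the random effect, this is a stated modelling choice and not merely an omitted detail.

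**Common practice.** A random-intercept model over three visits is widely used, and it agrees with the planning assumption of one correlation. Both are true. But the planning value is an input and not evidence about the trial's data. If the z scores are standardized within each visit, the variances would be roughly equal, but the correlations need not be.

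**Missing data.** A reader might also infer that a wrong covariance will bias the estimates when data are missing. It can in principle, but the article gives no dropout figures and no size can be put on it here.

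**Conclusion.** The point holds in a limited form. As written, the confirmatory model makes the week-8 SE depend on equal variances and equal correlations across three visits. If that fails, the SE can be about 10% too small to 17% too large, with a true two-sided level of about 2% to 8%. These figures rest on assumed SDs and correlations, complete data and a two-sided 5% test. With equal SDs and the common r = 0.5 of the Power Analysis section, the error is zero.

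The documents print no visit-specific SDs or correlations. They therefore do not show that the SE will be wrong, nor in which direction. The case for change is that the dependence is unnecessary and easy to remove. It is a cheap improvement, not a demonstrated error.

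**What to change.** Pre-specify for the primary model an unstructured 3×3 within-person covariance, fitted by REML with Kenward-Roger or Satterthwaite degrees of freedom. If it does not converge, fall back to a named simpler structure, such as heterogeneous compound symmetry, with a robust (sandwich) SE. State this in place of the random-intercept sentence, and say what the sentence on residual correlation refers to.

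The cost is one line of model specification and four more covariance parameters (six instead of two), which is negligible with 2 × 113 = 226 randomized participants. The unstructured form contains the stated model as a special case, so almost nothing is lost if compound symmetry is true. The Results section of the article reports that no data had been analysed. If that is still so, the change can be made before the analysis.
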